### Statistics and power calculations

For all power calculations, we will apply a level of significance of 0.05 and a power of 0.80, and the primary outcome is the degree of muscle hypertrophy determined as the change in quadriceps muscle CSA on MRI scans over the course of the 12-month intervention. On the basis of previous data [91], we set the following parameters: least average expected change over the course of the 12-month intervention between distinct intervention groups, 300 mm^2^ (corresponding to an estimated relative change of 6.5 %) with a SD set to 140 mm^2^. Our goal is to be able to detect differences between groups’ mean hypertrophy down to approximately 2 %, which corresponds to approximately 80 mm^2^. A difference in the change of quadriceps muscle CSA greater than 80 mm^2^ between any two groups is statistically detectable with a power of at least 0.80 with a group size of 30. We decided to include 35 subjects in each of the three groups (HRTW, LITW, and CARB), as we anticipated a dropout rate of 15 % at the time of study initiation. In the WHEY and COLL groups, we expected a larger dropout rate because of taste issues with protein supplements and no motivational effect by training as in the HRTW and LITW groups. Thus, we will include 50 each in the WHEY and COLL groups. On an ad hoc basis, we will evaluate the actual dropout rate and adjust the total number of inclusions accordingly.

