In a subset of participants from the five intervention groups, we will conduct experimental tracer studies before and after the 12-month intervention period to determine the extent to which the interventions affect the responsiveness of MPS to protein intake. The goal is to measure whether any of the interventions enhance the anabolic sensitivity to protein intake and thereby investigate if we can link the observed differences in muscle mass over the course of the intervention period to changes in the anabolic response to protein feeding. Thus, the outcome measure is the relative change in the FSR of muscle proteins from the basal condition, defined as the overnight fasted and resting state, to the average 4-h postprandial period after intake of a standard protein bolus. We are not aware of any data on changes in MPS responsiveness over time, and we therefore based the power calculations on a sum of our own published and unpublished data obtained in healthy elderly participants. We established the following parameters: expected average 4-h postprandial responsiveness to protein feeding from basal condition of 0.016 %/h (i.e., approximately corresponding to an increase in muscle protein FSR of 50 %) with an interparticipant SD on the increase of 0.017 %/h. We aim to be able to detect a 50 % change in responsiveness within a group over the course of the 12-month period (i.e., a change of 0.008 %/h in the increase in the muscle protein FSR from 0.016 %/h to 0.024 %/h). The SD for the change in responsiveness is set as 0.006 %/h. By including 10–12 participants, we obtain a power of at least 0.80 to detect a statistical difference over time within each intervention group. By taking the probability of dropouts into account, we decided to include 12 participants in the HRTW, LITW, and CARB groups and 15 in the WHEY and COLL groups, respectively.

Investigators will analyze data as intention-to-treat (except in subgroup analyses) as well as per protocol, and we will test the following groups against each other using one-way analysis of variance of the relative group changes from baseline to 12 months: (1) WHEY vs. COLL vs. CARB and (2) HRTW vs. LITW vs. WHEY. We will not conduct any interim analyses in this project.

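### The protein-synthesis sub-study's power of at least 0.80 rests on an SD of change (0.006 %/h) that, beside the protocol's between-person SD of 0.017 %/h, implies a 12-month test-retest correlation of about 0.94 and is shown without derivation

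*Protocol article*

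**What the plan says.** All of this is in the protocol article, section Statistics and power calculations.

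- **General rule:** for all power calculations, "we will apply a level of significance of 0.05 and a power of 0.80". Sidedness is not stated.
- **Sub-study outcome:** "Thus, the outcome measure is the relative change in the FSR of muscle proteins", from the fasted basal state to the 4-hour postprandial average.
- **Expected responsiveness:** 0.016 %/h, "with an interparticipant SD on the increase of 0.017 %/h".
- **Target within a group over 12 months:** "a change of 0.008 %/h in the increase in the muscle protein FSR from 0.016 %/h to 0.024 %/h".
- **Variability of that change:** "The SD for the change in responsiveness is set as 0.006 %/h".
- **Evidence base:** "We are not aware of any data on changes in MPS responsiveness over time". The sentence goes on to say that the calculations therefore draw on the authors' own published and unpublished data in healthy elderly people.
- **Claim:** "By including 10–12 participants, we obtain a power of at least 0.80 to detect a statistical difference over time within each intervention group".
- **Enrolment allowing for dropout:** 12 each in HRTW, LITW and CARB, and 15 each in WHEY and COLL.
- **Analysis:** the section closes with one rule for the trial, a one-way ANOVA of relative changes from baseline to 12 months across WHEY, COLL and CARB, and across HRTW, LITW and WHEY.

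**The concern.** Two SDs for the same quantity stand a few lines apart. One describes the spread of responsiveness between people on a single tracer day (0.017 %/h). The other describes the spread of its within-person change over a year (0.006 %/h), and it is about a third of the first. A change score is that much less variable than a single measurement only when the two occasions are very highly correlated.

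Responsiveness is itself a difference of two fractional synthesis rates (FSR), each built from enrichments in two biopsies and a precursor value (section Muscle protein synthesis). The 12-month change therefore combines four FSRs from two tracer days, and measurement error in each lowers the correlation. Different reactions to the intervention lower it further. The protocol gives neither a correlation nor the origin of 0.006.

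There is also a mismatch between the calculation and its use. The power is for an absolute change within one group. The stated analysis compares groups on relative changes.

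The sub-study involves an 8.5-hour infusion and three biopsies on each of two days, and its results are meant to help explain differences in muscle mass. If the power is overstated, a null result carries less information than the protocol suggests.

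**Working it through.** **Inputs.** From the protocol: change 0.008 %/h, SD of change 0.006 %/h, between-person SD 0.017 %/h, n = 10 to 12 (up to 15 enrolled in WHEY and COLL), alpha 0.05. Assumed here: two-sided testing and the values of the test-retest correlation r below 0.94.

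**Step 1. Reproduce the claim.** The paired t-test has df = n − 1 and noncentrality (0.008/SD) × √n. At SD 0.006 the standardised change is 0.008/0.006 = 1.33.

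- n = 7: power 0.83
- n = 10: 0.96
- n = 12: 0.99
- n = 15: above 0.99

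The claim of at least 0.80 is met with room to spare. Since 7 participants suffice, 10 to 12 is not the minimum for this test at this SD. It fits a paired test with SD 0.008 to 0.009, or a two-sample test at SD 0.006 (0.80 at n = 10, 0.88 at n = 12), so the basis of the number is unclear.

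**Step 2. Implied correlation.** With equal SDs on both occasions, SD of change = 0.017 × √(2(1 − r)). Hence r = 1 − 0.006² / (2 × 0.017²) = 1 − 0.000036/0.000578 = 0.938. If the 12-month SD s is left free, r = (0.017² + s² − 0.006²)/(2 × 0.017 × s). Its minimum over s is 0.936, so the result does not depend on equal variances.

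**Step 3. Within-group power for 0.008 %/h over a range of r.**

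| r | SD of change (%/h) | n = 10 | n = 12 | n = 15 |
|---|---|---|---|---|
| 0.94 (implied) | 0.0060 | 0.96 | 0.99 | >0.99 |
| 0.9 (assumed) | 0.0076 | 0.84 | 0.91 | 0.97 |
| 0.8 (assumed) | 0.0108 | 0.56 | 0.65 | 0.76 |
| 0.5 (assumed) | 0.0170 | 0.27 | 0.32 | 0.40 |

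For power 0.80 the SD of change may be at most 0.0080 at n = 10 (r about 0.89), 0.0090 at n = 12 (r about 0.86) and 0.0103 at n = 15 (r about 0.82).

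**Step 4. Detectable within-group change at power 0.80.** The change detectable at SD s is s × 0.008/(largest SD from step 3).

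| SD of change (%/h) | n = 10 | n = 12 | n = 15 |
|---|---|---|---|
| 0.006 | 0.0060 | 0.0053 | 0.0047 |
| 0.017 | 0.0169 | 0.0151 | 0.0132 |

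At the upper SD with 10 to 12 participants, the detectable change is about as large as the whole expected responsiveness of 0.016 %/h.

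**Step 5. Between-group power for a difference in change of 0.008 %/h.** Two-sample t-test, df = 2n − 2, noncentrality (0.008/SD) × √(n/2), for n = 10 and 12 per group.

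- SD 0.006: 0.80 and 0.88
- r = 0.8: 0.35 and 0.41
- r = 0.5: 0.17 and 0.20

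**Step 6. Relative change of responsiveness.** With mean 0.016 and SD 0.017, and if roughly normal, the share of participants with baseline responsiveness at or below zero is Φ(−0.016/0.017) = Φ(−0.94), about 17%. A percentage change from such a baseline has no stable meaning.

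**The case against.** The strongest reply is that nothing here is miscalculated. The protocol's inputs give its stated power, and an SD of change is a planning assumption that the authors may set. They cite their own published and unpublished data, which we cannot see and which may support 0.006. There is also margin: at n = 10 to 12 the SD may be 33 to 50% larger before power falls below 0.80. WHEY and COLL enrol 15, and dropout so far is 4.3% (Discussion). At r = 0.9 the claim holds at every planned size. The within-group power matches the sub-study's own stated aim, and the ANOVA sentence is the trial's general rule.

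Most of this stands, and it limits the point. A reader might infer that true power is only 0.27 to 0.65. The documents do not support that, because those figures need r between 0.5 and 0.8, which is our assumption, and no correlation for this measure is given. A reader might also infer that 0.006 has no data behind it. The text says only that the authors know of no data on change over time, so the fair statement is that no derivation is shown.

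The implied correlation of 0.94 survives the reply, because it follows from the protocol's own two SDs. The mismatch of scale and contrast also survives in part. The within-group aim is explicit, but the only analysis described is between groups. Where the wider aim is whether an intervention enhances anabolic sensitivity, a comparison of arms is needed. The relative-change wording might be read as loose, since the text equates 0.016 %/h with roughly a 50% rise in FSR, but the ANOVA sentence repeats it.

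**Conclusion.** The point holds as a doubt about an input, not as an arithmetic error. The stated power is correct if the SD of change is 0.006 %/h. Beside the between-person SD of 0.017 %/h, that value requires a 12-month correlation of about 0.94, whatever the 12-month variance. Power of 0.80 requires about 0.89 at n = 10, 0.86 at n = 12 and 0.82 at n = 15. Below those values the claim fails, and the lower rows of the table in step 3 show by how much. Which row applies cannot be settled from the protocol.

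The conclusion rests on two-sided testing and normality. One-sided testing would not change the picture: at n = 10 to 12, power runs from 0.39 (r = 0.5, n = 10) to 0.78 (r = 0.8, n = 12). The sub-study is a secondary outcome in a subset, and the primary cross-sectional-area outcome is untouched. A correction is worth making because the power figure is relied on for an invasive procedure and the change costs little.

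**What to change.** 1. State where 0.006 %/h comes from, or the correlation behind it. Restate power and detectable change over an SD of change from 0.006 to 0.017 %/h for n = 10, 12 and 15. Alternatively, take the SD from participants who have completed both tracer days, pooled and blind to arm. The Trial status section reports 54 completers of the intervention but not how many are in the tracer subset. A pooled SD compares no arms, so it need not breach the commitment to no interim analyses. It will be somewhat too large if arms differ in mean change.
2. Define responsiveness as the absolute increase, postprandial minus basal FSR in %/h, which is the scale of the power calculation.
3. Compare arms by ANCOVA of 12-month responsiveness with baseline responsiveness as covariate and arm as factor, in place of the ANOVA of relative changes for this outcome. Report within-group changes alongside, with confidence intervals, so that the stated aim is still served.

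The cost is a revised paragraph and at most one blinded SD calculation. All the data are already being collected, and no further participants or biopsies are needed. The downside is a less favourable stated power.

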### Measurements

This section describes each measurement performed to evaluate the longitudinal effects of the chosen interventions. Table 3 displays the time points for each examination. At baseline, we test the peak isometric and isokinetic peak torques as well as leg extensor power in both legs to evaluate if a large side difference between thigh peak torques is associated with an improved or diminished response to the interventions.

**Table 3 Tab3:** Time schedule of participant engagement

Measurement	Enrollment	Baseline	6 months	12 months	18 months	Other
Enrollment						
Recruitment and screening	X					
Information and consent	X					
Primary outcome						
MRI CSA of quadriceps femoris		X	X	X	X	
Secondary outcomes						
Thigh isometric peak torque		X	X	X	X	
Thigh isokinetic peak torque		X	X	X	X	
Thigh power		X	X	X	X	
30-second chair-stand		X	X	X	X	
Muscle biopsy		X		X		
Body composition (DXA)		X	X	X	X	
Bone mineral density (DXA)		X		X		
Gut microbiome		X	X	X		
Fecal metabolome		X	X	X		
Plasma metabolome		X	X	X		
Acute muscle FSR		X		X		
Tertiary outcomes						
Blood samples		X	X	X	X	
Anthropometry		X	X	X	X	
Hand grip strength		X	X	X	X	
400-m gait speed		X	X	X	X	
SF-36 and PSQI		X		X		
Activity monitoring		X	X	X	X	
Registration of food consumption		X		X		At week 6
Sensory questionnaires			X	X		Weekly for 0–3 months
Satisfaction with Food-related Life scale		X	X	X		
Oral glucose tolerance test		X		X		
Qualitative interview		X			X	
Questionnaire on food habits		X				
Life story interviews						Ad hoc
Ethnographic fieldwork						Ad hoc

*Abbreviations: MRI CSA* magnetic resonance imaging cross-sectional area, *DXA* dual-energy X-ray absorptiometry, *FSR* fractional synthesis rate, *PSQI* Pittsburgh Sleep Quality Index, *SF-36* 36-item Short Form Health Survey

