#### Primary outcome

A change in muscle CSA is a direct reflection of the intervention’s ability to restore muscle protein and a direct consequence of the net protein balance over time in the target muscles. We chose m. quadriceps and m. vastus lateralis CSA based on MRI scans of the dominant thigh as the primary outcome, as it directly reflects the intervention’s ability to counteract age-related loss of muscle mass. MRI scans have high sensitivity and validity in terms of lean mass in skeletal muscle [61], and previous researchers have considered this modality superior to DXA [62, 63].

Each scan consists of six axial slices, with the first slice placed in the medial tibia plateau. Each slide is 8 mm thick and separated by a 60-mm gap as shown in Fig. 4. The primary time interval for assessment is from baseline to 12 months.

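### The test named for the intention-to-treat analysis can use only participants with a 12-month scan and ignores the 6-month MRI, although dropout is expected to differ by arm

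*Protocol article*

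**What the plan says.** The last paragraph of Statistics and power calculations states the analysis sets, "Investigators will analyze data as intention-to-treat (except in subgroup analyses) as well as per protocol", and in the same sentence fixes the test as "one-way analysis of variance of the relative group changes from baseline to 12 months". It is applied to two three-group comparisons: WHEY, COLL and CARB; and HRTW, LITW and WHEY. Under Primary outcome: "The primary time interval for assessment is from baseline to 12 months".

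Table 3 (Measurements) marks the row "MRI CSA of quadriceps femoris" at baseline, 6, 12 and 18 months.

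On dropout, Statistics and power calculations assumes 15 % for HRTW, LITW and CARB and enrols 35 in each. For WHEY and COLL, "we expected a larger dropout rate because of taste issues with protein supplements and no motivational effect by training", and 50 are enrolled in each; no rate is given for these two arms. The Discussion gives 10–15 % as the rate first expected and 4.3 % as the loss so far, not split by arm.

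The second hypothesis (Working hypotheses) rests on the contrast between the two analysis sets. The advantage of heavy over light training is predicted per protocol but not under intention-to-treat, because adherence is presumed higher at home.

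**The concern.** An intention-to-treat comparison is meant to describe everyone randomised. The outcome in the named test is a change that needs both a baseline and a 12-month scan. Unless a value is imputed, a participant lost before month 12 contributes nothing, even if scanned at month 6. If those who leave would have done worse or better than those who stay, and leave at different rates by arm, the comparison of remaining participants is biased. Enrolling more people in the arms with more expected loss restores precision but does not remove that bias.

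The reasons given for extra loss in WHEY and COLL are taste and lack of a motivating training effect. Motivation could plausibly be related to outcome; taste may not be. Because WHEY belongs to both comparisons, both are exposed.

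**Working it through.** **The plan's own figures.** Inputs from Statistics and power calculations: "we will apply a level of significance of 0.05 and a power of 0.80"; a difference of 80 mm² "with a SD set to 140 mm^2"; 30 per group; enrolment of 35 or 50.

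- Enrolment: 30/(1 − 0.15) = 35.3, and 35 × 0.85 = 29.75, so 35 fits a 15 % loss closely. For WHEY and COLL, 1 − 30/50 = 0.40, so enrolling 50 would allow up to 40 % loss. Total: 3 × 35 + 2 × 50 = 205, as stated.
- Power, two-sided: 80/(140 × √(2/30)) − 1.96 = 2.21 − 1.96 = 0.25, which gives power 0.60, not 0.80. That is a separate matter on which this point does not depend.

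**Bias of a comparison restricted to those scanned.** If dropouts' mean change is k SD worse than that of completers, and the fraction lost is d, the completer mean exceeds the arm's full mean by d × k × 140 mm². The bias between two arms is therefore (d₁ − d₂) × k × 140. The values of k (0.25 and 0.5) are assumptions. Results are in mm² because the sample size is set in mm², although the named test uses relative change.

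| Dropout, arm 1 vs arm 2 | k = 0.25 | k = 0.5 | Basis for the rates |
|---|---|---|---|
| 40 % vs 15 % | 8.75 | 17.5 | 40 % is the most that enrolling 50 allows |
| 25 % vs 15 % | 3.5 | 7.0 | 25 % is assumed |
| 15 % vs 10 % | 1.75 | 3.5 | the range in the Discussion |
| 4.3 % vs 4.3 % | 0 | 0 | loss so far, if equal across arms |

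If the whole 4.3 % fell in WHEY and COLL, the rate there would be 0.043 × 205/100 = 8.8 % against 0 %, and the bias 0.088 × k × 140 = 3.1 to 6.2 mm².

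With dropouts worse than completers, the bias favours the arm that loses more: WHEY against CARB, HRTW and LITW. Between WHEY and COLL it cancels if rate and k are equal.

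**What the 6-month scan would recover.** A simulation of 4,000 runs compared WHEY (50 enrolled, 40 % lost) with CARB (35 enrolled, 15 % lost) under no true difference. Dropout was made likelier by a poor 6-month change, and the correlation between the 6- and 12-month changes was assumed to be 0.5 or 0.7.

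| Analysis | Bias, correlation 0.5 | Bias, correlation 0.7 |
|---|---|---|
| 12-month completers only | 14.0 mm² | 19.2–19.3 mm² |
| 6-month change used; half of dropouts have that scan | 4.4 mm² | 6.2 mm² |
| 6-month change used; all dropouts have that scan | −0.3 mm² | −0.8 mm² |

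Against 80 mm², the completer bias is 14.0/80 = 17.5 % to 19.3/80 = 24 %. The setting favours the model, because dropout depends only on a value that is observed when the 6-month scan exists.

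**The case against.** The article does not say that participants without a 12-month scan are left out. That is inferred from the test, and a fuller analysis plan could add imputation or a mixed model. This stands as a limit. The point is not that a missing-data section is absent, but that the test the article does name cannot by itself deliver the analysis it is labelled as.

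Three stronger readings are tempting and not supported.

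- *The inflated sample size shows that dropouts are excluded.* It does not. Trials enrol extra participants for expected loss whatever the analysis method, because missing outcomes cost information.
- *The intention-to-treat and per-protocol contrast in the second hypothesis collapses.* It does not. Adherence is recorded separately, in diaries and by trainers (Interventions), and nothing says that those who stop training are not scanned. Non-adherent participants who are scanned stay in the intention-to-treat comparison. No difference in dropout between HRTW and LITW is stated.
- *The bias in HRTW can be found by multiplying 300 mm² by a non-adherent share.* The 300 mm² is an expected difference between groups, not the gain of adherers. The only rate stated for HRTW is 15 %. Even that would give 300 × 0.15 = 45 mm² only if every such participant were unscanned and gained nothing.

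The low loss so far also counts against a large effect. It is an early figure, however: 4.3 % of about 150 is 6 to 7 people, at a time when 54 had completed the intervention (Trial status). If all those losses came from participants who would by then have reached month 12, the rate is 6.5/(54 + 6.5), or about 11 %, a rough ceiling.

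**Conclusion.** The point holds in a limited form. As named, the intention-to-treat test compares those with a 12-month scan and discards a 6-month scan that is already scheduled, in a trial that expects arm-dependent loss. Both comparisons are exposed through WHEY.

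The likely bias is modest and uncertain: about 9–19 mm² on the 40 % against 15 % assumption, 3.5–7 mm² at 25 % against 15 %, and little at the loss seen so far. The 40 % is only what enrolling 50 would allow, and it does not fit the 10–15 % that the Discussion reports as first expected. All these sizes rest on assumed differences between dropouts and completers, or on assumed correlations, which the documents do not give. If dropout is unrelated to outcome, for instance purely a matter of taste, there is no bias.

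The contrast behind the second hypothesis is weakened only to the extent that those who stop training also miss the 12-month scan. The change is still worth making, because the replacement is better and uses data already planned.

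**What to change.** - Replace the ANOVA, for the intention-to-treat analysis, with a longitudinal mixed model of CSA at baseline, 6 and 12 months, with arm-by-time terms and adjustment for sex and chair-stand class (the stratification factors under Randomization). Make the 12-month arm contrasts primary. If relative change is to be kept, model log CSA.
- State that the 6- and 12-month MRI is sought from every randomised participant regardless of adherence.
- Keep the change-score ANOVA if wanted, but call it a completer analysis.
- Add one sensitivity analysis for missing 12-month scans, for example setting the unobserved changes 35 to 70 mm² (0.25 to 0.5 × 140) worse than the model predicts.

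The cost is revised wording, slightly more analysis work and effort to bring discontinuers to visits already in Table 3. Of 153 randomised, 54 had completed the intervention, so many 12-month scans could still be secured. The model does little for those who leave before month 6, so the follow-up effort matters as much as the choice of model.

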### Working hypotheses

We designed the CALM Intervention Study to investigate two overarching working hypotheses:

1. Whey protein hydrolysate supplementation is more efficient than collagen protein hydrolysate and carbohydrate in improving muscle size when administered to healthy elderly individuals.

2. With whey protein hydrolysate supplementation, the addition of center-based heavy resistance training is advantageous to home-based light load resistance training, and both of these regimens are superior to no training at all, in regard to improving muscle mass, overall health, and physiological parameters only with a per-protocol analysis. This will not be the case in regard to intention-to-treat analysis, where a markedly higher adherence is presumed in the home-based training group, leading to a similar or superior response compared to the center-based heavy resistance training group.

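### One-way ANOVA assumes equal variances across arms, but under Hypothesis 2 heavy training is plausibly the most variable arm by intention to treat; Welch's form would cost almost nothing

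*Protocol article*

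**What the plan says.** The Statistics and power calculations section of the protocol article names the test: "we will test the following groups against each other using one-way analysis of variance". The outcome is the relative change from baseline to 12 months. The second of its two three-arm sets is HRTW, LITW and WHEY, analysed by intention to treat and per protocol.

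The same section plans with one spread for every arm: "300 mm^2^ (corresponding to an estimated relative change of 6.5 %) with a SD set to 140 mm^2". HRTW and LITW enrol 35 each. For the untrained whey arm, "we will include 50 each in the WHEY and COLL groups".

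Hypothesis 2 (Working hypotheses) expects heavy training to beat light training per protocol. By intention to treat it expects this advantage to disappear or reverse, "where a markedly higher adherence is presumed in the home-based training group". No adherence rate and no arm-specific SD is given.

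**The concern.** The hypothesis and the test fit poorly together. If heavy training works better in those who do it but fewer people do it, the intention-to-treat HRTW arm mixes large responders with people who respond little. Such a mixture has a larger variance than either part. An ordinary one-way ANOVA averages that variance with those of LITW and WHEY, and WHEY, the largest arm, has no training-adherence mixture.

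A common error term is then too small for contrasts involving HRTW and too large for LITW against WHEY. The first includes HRTW against LITW, on which Hypothesis 2 turns. The second is the comparison that would support home-based training over no training.

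**Working it through.** **Inputs from the article (Statistics and power calculations).** Alpha 0.05; SD 140 mm²; expected change 300 mm²; detectable difference 80 mm²; 30 per group for power; enrolment 35/35/50 in HRTW/LITW/WHEY.

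**Assumptions, not in the article.** Two-sided tests; all-or-none adherence; adherers in HRTW gain D = 300 mm² over non-adherers; HRTW adherence a = 0.5–0.8; LITW adherence 0.95; equal intention-to-treat means; WHEY SD 140.

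**1. The plan's own figure.** The article claims detection of 80 mm² "with a power of at least 0.80 with a group size of 30". The difference has standard error 140 × √(2/30) = 36.1. Then 80/36.1 = 2.21, and Φ(2.21 − 1.96) = 0.60 (0.59 with the noncentral t). The stated power is not reproduced. That is a separate matter, but it rests on the same single SD.

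**2. Variance of a mixed arm.** Variance = 140² + a(1 − a)D².
- HRTW, a = 0.5: √(19,600 + 22,500) = 205
- a = 0.6: √(19,600 + 21,600) = 203
- a = 0.7: √(19,600 + 18,900) = 196
- a = 0.8: √(19,600 + 14,400) = 184

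With mean m = aD the added term equals m(D − m). If two arms share the same m, the arm with the larger D has the larger variance. Under Hypothesis 2 that arm is HRTW, whatever the exact rates.

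**3. One case in full (a = 0.7).** m = 210. LITW needs D = 210/0.95 = 221, so its variance is 19,600 + 0.95 × 0.05 × 221² ≈ 21,920 (SD 148).

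Pooled variance = (34 × 38,500 + 34 × 21,920 + 49 × 19,600)/117 ≈ 25,770 (SD 160.5).

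| Contrast | Pooled SE | True SE | Ratio |
|---|---|---|---|
| HRTW − LITW | 38.4 | 41.5 | 0.92 |
| HRTW − WHEY | 35.4 | 38.6 | 0.92 |
| LITW − WHEY | 35.4 | 31.9 | 1.11 |

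**4. Error rates at nominal 5%.** Simulation, 40,000 trials per setting, a = 0.5–0.8, arms 35/35/50:

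| Test | Pooled variance | Welch |
|---|---|---|
| Omnibus, three arms | 5.9–6.4% | about 5% |
| HRTW − LITW, unadjusted | 6.7–7.4% | about 5% |
| HRTW − WHEY, unadjusted | 6.6–7.9% | about 5% |
| LITW − WHEY, unadjusted | 2.5–3.7% | about 5% |

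**5. How far this moves.**
- At 30 per arm the omnibus test is at 5.3–5.4%. The pooled-error contrasts stay distorted: 6.3–6.9%, 5.7–6.6% and 2.1–3.3% in the same order.
- With graded (beta-distributed) adherence at 35/35/50, the two HRTW contrasts fall to about 5.5–6.4%.
- With D = 300 and 200 mm² and adherence 0.1 and 0.5, the SDs are 166 (HRTW), 172 (LITW) and 140 (WHEY), so HRTW is no longer the most variable. The intention-to-treat means are then 30 and 100, clearly favouring LITW.
- An extreme reading takes 300 mm² as the gap between neighbouring arms (D = 600 and 300, adherence 0.45 and 0.9). The SDs are 330/166/140, and the omnibus test is at 8.4%.

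**6. Price of Welch if variances are equal.** At 30 per group and 80 mm²: power 0.584 pooled, 0.583 Welch.

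**The case against.** The strongest reply is that the article names only a three-arm one-way ANOVA. It states no variance assumption, no follow-up contrasts and no intervals. Welch's test is itself a one-way ANOVA, and such detail may sit in an analysis plan that is not shown. The only test actually named is off by about one percentage point. The contrast rates depend on the follow-up chosen. A pooled two-sample t test of HRTW against LITW, using those two equal arms alone, is at about 5%. This stands as a limit on size. It does not remove the point:
- The unqualified name ordinarily means the pooled test, and the planning SD is also common to all arms.
- The two-sample t test of HRTW against WHEY still runs at 6.2–6.7%.
- Bonferroni on the pooled error gives 2.6–2.9% for HRTW against LITW, below 5% but above its own per-comparison level of 5%/3 = 1.7%.

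It is also fair that 300 mm² is described as a difference between groups rather than a gain in adherers. The 140 mm² may already contain variable adherence, and WHEY may have its own non-adherence to the supplement. Each of these could narrow the gap. The check is in absolute mm² while the planned analysis uses relative change. By the article's own figures 300 mm² is 6.5%, so the conversion is mainly a change of scale.

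Two stronger readings are tempting. A reader might infer that the adherence hypothesis guarantees the largest variance in a uniquely small HRTW arm. It does not: the ordering needs roughly similar intention-to-treat means, Hypothesis 2 also allows a superior LITW response, and LITW is just as small. A reader might also infer that precision is understated for light training in general. That holds for LITW against WHEY; for HRTW against LITW the pooled error is too small.

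**Conclusion.** The point holds in a conditional and modest form. The named test, in its ordinary form, makes an equal-variance assumption that the trial's own hypothesis gives reason to doubt for the intention-to-treat comparison of HRTW, LITW and WHEY.

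If adherence is all-or-none and means are similar, the omnibus error is about 6%. Any unadjusted contrast on the three-arm error is somewhat anti-conservative when HRTW is involved and conservative for LITW against WHEY. The documents do not support saying that the plan will declare a heavy–light difference too often, because they name no pairwise procedure. The matter is minor to moderate, and worth acting on because the remedy is nearly free.

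**What to change.** In Statistics and power calculations, replace the unqualified one-way ANOVA with Welch's one-way ANOVA, followed by separate-variance (Welch) contrasts for the stated comparisons. If covariates are added, fit the corresponding linear model with an arm-specific residual variance. If a Welch form is already intended, say so.

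The cost is one sentence. No data collection changes, and there is practically no loss of power if the variances prove equal.
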